**Figure 2. f2:**
[figure not shown]
Study outline. The study includes four in-clinic visits separated by observation periods with daily prospective eDiary recording.

Considerations for woman of childbearing potential

This study will include women of childbearing potential irrespective of contraceptive use, as well as pregnant and breastfeeding women. In accordance with Article 66 of the Medical Device Regulation (MDR 2017/745), pregnant and breastfeeding participants require additional protection, including specific justification and risk minimisation measures where appropriate.

In chronic migraine, only CGRP-targeting treatments, topiramate, and onabotulinumtoxinA are supported by high-quality clinical evidence. Topiramate has recently fallen out of favour for women of childbearing potential due to the risk of neurodevelopmental disorders [12], while the safety of onabotulinumtoxinA and CGRP-inhibitors during pregnancy remains unknown, rendering them contraindicated. Consequently, effective prophylactic options are highly limited during the period when women are trying to conceive and throughout pregnancy.

Local anaesthesia administered towards the greater occipital nerve (GON) either as part of the conventional GON block or as anaesthesia as part of the CryoGON procedure, is not contraindicated in these populations, and conventional GON blocks are already in clinical use in pregnant and breastfeeding patients.
^
18–
20
^ Cryoneurolysis is a non-pharmacological treatment, not contraindicated in these populations, and there is no plausible rationale to suspect increased risk of harm to a nursing child or an embryo or fetus. Given the very limited alternative treatment options available, inclusion of pregnant and breastfeeding participants in this study is considered acceptable.

### Study procedure

Conventional GON-block

The conventional GON block will be performed bilaterally in an outpatient setting by trained investigators. The injection site is identified at the medial third of a line drawn between the external occipital protuberance and the mastoid process. After sterile skin preparation, a 23-gauge needle attached to a 5 mL syringe is inserted perpendicular to the skin until firm resistance is encountered, indicating contact with the periosteum. The needle is then withdrawn slightly, aspiration is performed to exclude arterial entry, and the needle is redirected superiorly.

A total of 4 mL per side of a 50:50 mixture of lidocaine 2% and bupivacaine 0.5% is injected slowly in a fan-shaped distribution to ensure adequate spread. The procedure is repeated contralaterally.

### CryoGON-procedure

The CryoGON procedure will be performed as an image-guided, percutaneous intervention. Image modalities may be per-procedural ultrasound guidance and/or surgical navigation based on MRI neurography. Devices will be used in accordance with their intended purpose and instructions for use (IFU). Study interventionists are trained surgeons with prior experience using navigation and cryoneurolysis technology and will perform the procedure according to the IFU.

For each procedure, local anesthetics will first be administered with 2–8 mL of lidocaine/adrenaline. A small skin incision of approximately 2 mm is then made at the predetermined entry point near the GON. The cryoprobe is advanced towards the target nerve under image guidance using the navigation system. Once appropriate positioning is confirmed, cryoneurolysis is applied in three cycles of 1 minute each, after which the probe is carefully retracted.

To ensure procedural consistency, the intervention will be standardised prior to study initiation. Core procedural elements, including patient positioning, target definition, cryoablation parameters, and post-procedural assessment, will be predefined. An operation form documenting all procedural elements will be completed for each intervention, and any deviations from the predefined procedure will be prospectively recorded and reported.

Participants will be observed 30 minutes post-procedure to monitor for acute adverse events and discharged home thereafter.

### Safety

Clinical experience spanning nearly half a century supports the safety of cryoneurolysis as a therapeutic approach in pain management.
^
21–
23
^ Known adverse device effects include injection site bleeding, hematoma and bruising. Injection site infection is reported as very rare.
^
24,
25
^ In contrast to other neuroablative methods, cryoneurolysis has demonstrated a low risk for neuritis, and if it occurs, it is transient. However, transient dysesthesia of a severity that affectes activities of daily living has been reported, occurring in 1,2% in one study.
^
26
^ Long term neuropathy induced by cryoneurolysis has never been reported.
^
21,
23
^ Treatment of superficial nerves can cause hyperpigmentation, depigmentation and alopecia at the treatment site, and excessively superficial lesioning can cause skin frostbite.
^
23
^ In five studies that targeted the occipital nerve,
^
14–
16,
27,
28
^ reporting from a total of 172 participants, mostly minor and transient adverse events occurred. One hematoma and 2 postprocedural occipital neurits were reported.
Table 2 presents a list of known or anticipated adverse device effects associated with cryoneurolysis.

**Table 2. T2:** Known or anticipated adverse device effects associated with cryoneurolysis. MedDRA = Medical dictionary for regulatory activities, TEAE = Treatment emergent adverse events.

MedDRA lowest level term	MedDRA code
**TEAE related to the area of administration of the CryoGON-procedure **	
Administration site infection	10066214
Administration site erythema	10074796
Administration site pain	10058049
Administration site swelling	10075107
Administration site pruritus	10075106
Administration site hyperpigmentation	10079246
Administration site hypopigmentation	10079247
Administration site bruise	10075094
Administration site haematoma	10075100
Administration site erosion	10075931
Administration site indentation	10079277
Administration site haemorrhage	10075101
**TEAE related to postprocedural disturbed occipital nerve function (i.e. not restricted to site of administration but the nerve sensory distribution area)**	
Neuropathic pain	10054095
Paraesthesia	10033775
Dysaesthesia	10013886
Hyperaesthesia	10020568
Allodynia	10053552
Hypoaesthesia	10020937
Anaesthesia	10002091

### Data collection

A predefined source data list will specify what constitutes source data in this investigation. Source documentation includes electronic patient records (EPJ) for medical history, eligibility assessments, medication use (including preventive treatments), headache diagnoses, and safety data. Data handling will comply with the General Data Protection Regulation (GDPR) and institutional requirements. Study data will be retained for 25 years after completion, as mandated by Norwegian law. Data management will follow a study-specific data management plan.

*eCRF*

An electronic Case Report Form (eCRF) will be implemented using the VieDoc™ platform (Viedoc Technologies AB), supported via the research department at St. Olav’s University Hospital. Information obtained during visits, telephone consultations, and all safety events will be entered into the eCRF. Data are stored in a pseudo-anonymised format, where participants are identified only through a unique study identification number. In case of active withdrawal, the reason (if any) will be registered in the eCRF.

*eDiary*

The eDiary application serves as the primary tool for endpoint data collection. Participants will complete daily entries throughout the baseline, GON-block, and CryoGON follow-up periods, regardless of headache status. On headache days, participants report maximum pain intensity, duration, the presence of aura, abortive medication use, and whether the headache is a migraine. A section to report alteration in participant health (e.g. potential adverse events) is available every day.

Investigators access an online dashboard that enables monitoring of diary adherence and identification of participants with insufficient entries. Entries can be made retrospectively for up to three days (current day plus the two preceding days).

*Safety data*

Safety data are collected through structured interviews at visits and telephone follow-ups, and in case of participants making contact in-between. The online dashboard presents patient-reported potential adverse events from the eDiary, which will be reviewed during study contacts. All treatment-emergent adverse events (AEs) will be registered in the eCRF.

*Questionnaires*

The Migraine-Specific Quality of Life Questionnaire v2.1(MSQ) and the Patients’ global impression of change (PGI-C) will be administered to participants. The MSQ will be collected at baseline and at week 12 following CryoGON. The PGI-C will be collected at day 1 and week 4 following conventional GON and week 8 and 12 following the CryoGON-procedure. All copyrighted instruments will be used with proper permission or license.

## Study endpoints and endpoint variables

Endpoint variable definitions follow the International Headache Society (IHS) guideline for controlled trials of preventive treatment of chronic migraine
^
17
^ (
Table 3). The primary endpoint variable for this study is moderate to severe headache days. Several endpoints (
Table 4) are predefined to address the two main objectives of the study, i.e. assessing whether short-term response to a conventional GON block predicts subsequent response to CryoGON and evaluating the clinical performance of the CryoGON procedure.

**Table 3. T3:** Overview of endpoint variable definitions.

Variable	Definition
Moderate–severe headache day	A moderate/severe headache day is defined as a day with moderate or severe pain that lasts at least 4 hours or a day with a headache that is successfully treated by an acute headache medication.
CryoGON responder (≥30%; ≥50%)	≥30% or ≥50% reduction in moderate–severe headache days from baseline to weeks 9–12 after CryoGON.
GON block responder (≥30%; ≥50%)	≥30% or ≥50% reduction in moderate–severe headache days from baseline to weeks 1–4 after conventional GON block.
Self-reported migraine day	Any calendar day with ≥4 hours of headache and a participant-reported classification as a migraine, or any day with headache that is successfully treated with a triptan and/or gepant. For self-classification, participant are instructed to adhere to the following migraine day definition: A calendar day with a headache that lasts at least 4 hours; meets ICHD-III criteria C and D for migraine without aura (1.1), B and C for migraine with aura (1.2), or ICHD-III criteria for probable migraine (1.6); or a day with a headache that is successfully treated with a triptan and/or gepant.
Acute medication use	Number of days with use of acute medications per 28-day period. Analgesics used only for other purposes than headache treatment are not included.
Headache intensity	Maximum headache intensity is recorded on every day with headache at a 0-10 numerical rating scale.
MSQ v2.1	Migraine-Specific Quality of Life Questionnaire v2.1 (MSQ v2.1). The MSQ is copyrighted and registered with the United States Library of Congress by Glaxo Wellcome, Inc. MSQ v2.1 has undergone a formal translation process to Norwegian according to linguistic validation methodology. Permission for use will be obtained via Mapi Research trust before study initiation.
PGI-C	Patients’ global impression of change (PGI-C) questionnaire is public domain. PGI-C has undergone a formal translation process to Norwegian according to linguistic validation methodology.
AE	Defined according to MDR (EU 2017/745) Art. 2(57).
SAE	Defined according to MDR (EU 2017/745) Art. 2(58).
Treatment-emergent	Refers to AE that occur during or in a prespecified interval after the intervention (separately tabulated for CryoGON (occurring week 1-12 after procedure) and GON block (occurring week 1-4 after injection).
AE severity	CTCAE v6.0 grade 1-5: **Grade 1** Mild; asymptomatic or mild symptoms; clinical or diagnostic observations only; intervention not indicated. **Grade 2** Moderate; minimal, local or noninvasive intervention indicated; limiting age- appropriate instrumental ADL*. **Grade 3** Severe or medically significant but not immediately life-threatening; hospitalization or prolongation of hospitalization indicated; disabling; limiting self care ADL**. **Grade 4** Life-threatening consequences; urgent intervention indicated. **Grade 5** Death related to AE.
AE relationship assessment	The following categories from the MDCG 2020-10/1 Rev 1 will be used: **Not related:** Relationship to the CryoGON procedures can be excluded when: - the event has no temporal relationship with the procedure; - the serious adverse event does not follow a known response pattern to procedure and is biologically implausible; - the event involves a body-site or an organ that cannot be affected by the device or procedure; - the adverse event can be attributed to another cause (e.g. an underlying or concurrent illness/clinical condition, an effect of another device, drug, treatment or other risk factors. **Possible:** The relationship with the CryoGON procedures, is weak but cannot be ruled out completely. Alternative causes are also possible (e.g. an underlying or concurrent illness/clinical condition or/and an effect of another device, drug or treatment). **Probable:** The relationship with the CryoGON procedure seems relevant and/or the event cannot be reasonably explained by another cause. **Causal relationship:** the adverse event is associated with the CryoGON-procedure beyond reasonable doubt when: - the event is a known side effect of the any element of the procedure, including cryoneurolysis, or of similar devices and procedures; - the event has a temporal relationship with the procedures; - the event involves a body-site or organ that the procedure is applied to or the procedure have an effect on; - the adverse event follows a known response pattern to cryoneurolysis, - other possible causes (e.g. an underlying or concurrent illness/clinical condition or/and an effect of another device, drug or treatment) have been adequately ruled out; - harm to the subject is due to error in use Cases where relatedness cannot be assessed, or no information has been obtained will be classified as possible.
ADE	Any TEAE with possible, probable or causal relationship to the procedure.
SADE	Any TESAE with possible, probable or causal relationship to the procedure.
Procedural pain (tolerability)	NRS 0–10 discomfort during CryoGON; recorded immediately post-procedure.
Willingness to repeat (tolerability)	Participant-reported willingness to repeat CryoGON (yes/no/unsure) considering experienced benefits and drawbacks.
Technical success	Technical success is a composite (i) surgeon-confirmed completion of planned lesion at intended target with no device deficiency; (ii) Participant-reported numbness lasting >72 hours within the expected bilateral GON sensory distribution.
Device deficiency	Defined according to MDR (EU 2017/745) Art. 2(59) as any inadequacy of the medical devices used during the CryoGON procedure with respect to its identity, quality. durability, reliability, usability, safety or performance, and includes malfunctions, user errors and inadequacy in the information supplied by the manufacturer including labelling.
Procedure time	Elapsed time, measured in whole minutes, from the moment the participant enters the procedure room until the moment the participant leaves the room following completion of the CryoGON intervention.
Diary adherence	Proportion of days with completed eDiary entries per 28 day period.

GON = Greater occipital nerve, CryoGON = Cryoneurolysis of the GON, AE = Adverse event, SAE = Serious AE, ADE = Adverse device effect, SADE = Serious ADE, MDR = Medical device regulation.

**Table 4. T4:** Overview of study endpoints.

Objective	Outcome measure	Endpoint definition	Time point
**Primary prediction endpoint**			
Evaluate whether response to a conventional GON (cGON) block predicts response to CryoGON	Change in moderate–severe headache days	Change from baseline to weeks 9–12 after CryoGON; modelled on change after GON block (weeks 1–4) as primary predictor	Baseline; weeks 1–4 (cGON); weeks 9–12 (CryoGON)
**Key secondary prediction endpoints**			
Evaluate the clinical utility of GON block as a predictor (≥30% threshold)	Dichotomised responder status (≥30%)	Proportion achieving ≥30% reduction from baseline to weeks 9–12 after CryoGON; predictor is proportion achieving ≥30% after GON-block (weeks 1–4).	Baseline; weeks 1–4 (cGON); weeks 9–12 (CryoGON)
Evaluate the diagnostic accuracy at 30% responder threshold	Sensitivity, specificity, PPV, NPV	Metrics derived from 2×2 table comparing GON-block responder (yes/no) vs CryoGON responder (yes/no) with 95% CIs.	Weeks 1–4 (cGON) and weeks 9–12 (CryoGON)
**Other secondary predication endpoints**			
Evaluate the clinical utility of cGON block as a predictor (≥50% threshold)	Dichotomised responder status (≥50% responder)	Proportion achieving ≥50% reduction from baseline to weeks 9–12 after CryoGON; predictor is proportion achieving ≥50% after GON-block (weeks 1–4).	Baseline; weeks 1–4 (cGON); weeks 9–12 (CryoGON)
Evaluate the diagnostic accuracy at 50% responder threshold	Sensitivity, specificity, PPV, NPV	Metrics derived from 2×2 table comparing GON-block responder (yes/no) vs CryoGON responder (yes/no) with 95% CIs.	Weeks 1–4 (cGON) and weeks 9–12 (CryoGON)
Evaluate the clinical utility of cGON block as a predictor (global impression of change threshold at 4 week)	Dichotomised responder status (improvement on PGI-C)	Proportion reporting improvement on PGI-C after CryoGON (week 12); predictor is the proportion reporting improvement on PGI-C after conventional GON (at week 4).	For CryoGON: At week 12 or earlier in case of study withdrawl. For cGON, at week 4
Evaluate the clinical utility of cGON block as a predictor (global impression of change threshold at day 1)	Dichotomised responder status (improvement on PGI-C)	Proportion reporting improvement on PGI-C after CryoGON (week 12); predictor is the proportion reporting improvement on PGI-C after conventional GON (at week 4 the day after procedure).	For CryoGON: At week 12 or earlier in case of study withdrawl. For cGON, at day 1
Evaluate the diagnostic accuracy, applying impression of change threshold	Sensitivity, specificity, PPV, NPV	Metrics derived from 2×2 table comparing GON-block responder (yes/no) vs CryoGON responder (yes/no) with 95% CIs.	Week 4 or day 1 (cGON), Week 12 (CryoGON)
**Primary safety endpoint**			
Evaluate the safety of CryoGON	ADEs and SADEs (device-related, treatment-emergent) number and severity	Number of SADEs Number of ADEs and proportion for each ADE with different CTCAE grad (1-5)	Procedure → Week 12

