Tolerability will primarily be evaluated by intra-procedural discomfort (NRS 0–10) and additionally, the willingness of the participant to repeat the CryoGON procedure. At week 12, or earlier in the event of participant withdrawal, participants will be explicitly asked to consider the balance of perceived benefits and drawbacks of CryoGON and respond with ‘yes’, ‘no’, or ‘unsure’ regarding willingness to undergo the procedure again. The primary feasibility endpoint will be technical success rate. Technical success is defined as a composite of (i) surgeon-confirmed completion of the planned cryo-lesion at the intended target without device deficiency, and (ii) participant-reported numbness persisting >72 hours in the GON peripheral innervation area as reported by the participant on a telephone call after one week. The second criterium is included with the intention to distinguish prolonged sensory change consistent with cryoneurolysis from transient anaesthesia due to local anaesthetic used during the procedure. Other feasibility endpoints are number of device deficiencies, CryoGON procedure duration and diary adherence across study periods.

Adequate diary adherence is essential for the valid estimation of headache day–based endpoints, particularly responder rates. Therefore, diary adherence is included as an operational feasibility endpoint to enable evaluation of the robustness of the data underpinning both the primary endpoint and the open-label efficacy analyses.

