### Subgroup analysis

Subgroup analyses will be prespecified in the SAP, and may include exploring differences in effect according to the degree of numbness following CryoGON (hypoaesthesia vs anaesthesia) and comparing bilateral versus unilateral successful CryoGON treatment.

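### Numbness in the GON area is both required for technical success and listed as an adverse device effect, so the aggregate ADE count largely tracks successful lesioning

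*Protocol article*

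**What the plan says.** Five parts of the protocol article bear on this.

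- **Technical success** (Table 3; also Table 4, primary feasibility endpoint). The second criterion is "Participant-reported numbness lasting >72 hours within the expected bilateral GON sensory distribution". The section on open-label clinical performance explains that this criterion is there "to distinguish prolonged sensory change consistent with cryoneurolysis from transient anaesthesia due to local anaesthetic used during the procedure". Numbness is thus the sign that the intended lesion was made.
- **Words for numbness** (Subgroup analysis). A possible subgroup is the "degree of numbness following CryoGON (hypoaesthesia vs anaesthesia"). The protocol therefore describes this numbness with these two terms.
- **Adverse device effects** (Safety, Table 2). The table is introduced as a list of "known or anticipated adverse device effects associated with cryoneurolysis". Its second block, "TEAE related to postprocedural disturbed occipital nerve function", covers the nerve's sensory area and includes both Hypoaesthesia and Anaesthesia.
- **ADE definition** (Table 3). An ADE is "Any TEAE with possible, probable or causal relationship to the procedure". The text on safety endpoints gives the same rule. Neither makes an exception for an expected or intended effect.
- **Primary safety endpoint** (Table 4). It consists of the number of SADEs and "Number of ADEs and proportion for each ADE with different CTCAE grad (1-5"), from the procedure to week 12.

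The plan also summarises adverse events by MedDRA lowest level term and has a secondary safety endpoint for the average number of days with numbness.

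**The concern.** The finding that marks a successful procedure for the primary feasibility endpoint is also an event for the primary safety endpoint. If numbness is recorded as Table 2 suggests, the total number of ADEs rises with technical success. A series in which the nerve was often missed would show fewer ADEs and look safer, with no difference in unintended harm.

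The protocol also does not say outright whether numbness reported for the success criterion is entered as an adverse event. If practice differs between investigators or over time, the contribution of numbness could lie anywhere between none and one or more per participant. The total would then also reflect recording habits.

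At stake is how the total will be read, both in the report and when it is used to judge whether a sham-controlled trial is justified. One secondary endpoint is affected too: grade 1 treatment-emergent events are reported if they occur in at least 4% of participants, and grade 1 numbness would pass that threshold by design.

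**Working it through.** The protocol states no ADE rate or count, so there is no figure of its own to reproduce. The check is a reading of the definitions, followed by a count.

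**1. The chain of definitions.** Technical success requires numbness for more than 72 hours in the GON area. The protocol describes this numbness as hypoaesthesia or anaesthesia. Both are labelled treatment-emergent adverse events and anticipated device effects in Table 2. Numbness from a cryo-lesion would be judged related to the procedure, and every related treatment-emergent event is an ADE. So each technical success implies at least one ADE. The one link that is implied rather than stated is that each such report is entered as an adverse event.

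**2. The floor under the total.** Let T be the number of technically successful participants, with one numbness ADE each. Then the floor is T × 1. Sensitivity analyses says recruitment continues until the technical success set reaches the size given by the power calculation, which can be read in three ways from Sample size:

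- T = 70 (target sample size): at least 70 ADEs
- T = 31 (responder comparison, 18 + 13): at least 31
- T = 26 (regression slope): at least 26

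**3. The share of the total.** Let m be the number of other ADEs per participant. The documents do not give m, so a range is assumed. Among T participants, share = T / (T + mT) = 1 / (1 + m), which does not depend on T. For T = 70:

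- m = 0.1: 70 / (70 + 7) = 91%
- m = 0.25: 70 / (70 + 17.5) = 80%
- m = 0.5: 70 / (70 + 35) = 67%
- m = 1.0: 70 / (70 + 70) = 50%

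**4. Dependence on technique at constant harm.** Take 70 treated participants and hold other ADEs at an assumed 0.25 each (17.5 expected). Let the assumed technical success rate vary, counting numbness only in successes:

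- 60%: 42 + 17.5 = 59.5
- 80%: 56 + 17.5 = 73.5
- 95%: 66.5 + 17.5 = 84

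The expected total rises from 59.5 to 84, a factor of 1.41, while the other events do not change.

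**5. The 4% threshold.** 4% of 70 is 2.8, so three participants with grade 1 numbness are enough for it to be reported.

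**6. What is unaffected.** Separating numbness takes its floor in the total from at least 70 to 0 for T = 70. The SADE count and the lines for the other ADE terms do not change.

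**The case against.** The strongest reply is that the endpoint is not a bare total. Table 4 also gives SADEs and a breakdown of each ADE by CTCAE grade, and events are summarised by lowest level term. Hypoaesthesia and anaesthesia therefore stand on their own lines, apart from neuropathic pain, dysaesthesia, allodynia, haematoma and infection, and numbness duration is a separate endpoint. This stands. A reader might infer that the primary safety endpoint cannot describe unintended harm at all; the documents do not support that.

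A second reply is that a subtotal without two terms is table layout and can wait for the statistical analysis plan. This stands only in part. Per-term event lines can be added up, but they do not give the number of participants with at least one other ADE, because one person may have several. Nor can a plan finalised just before data lock recover numbness that was recorded inconsistently. The overlapping definitions are all fixed in this document.

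A third reply is that adverse events are defined by reference to the Medical Device Regulation, and nothing says that every numbness report becomes one. That is correct, so the floor is conditional. It is also a reason to state the rule.

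A fourth is that counting every related event is the cautious choice, and that removing sensory loss from the main figure could hide severe or lasting loss. This is a fair warning, and the remedy must keep the all-ADE total and show sensory loss in full.

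**Conclusion.** The point holds for the aggregate number of ADEs. As the definitions stand, that number would contain at least one event per technically successful participant: at least 70, or 26 or 31 under the other readings of the recruitment rule. At an assumed 0.1 to 1.0 other ADEs per participant, numbness would be about 91% to 50% of it. The assumptions are that each such report is recorded as an adverse event, that it counts once per participant, and that the unknown rate of other ADEs lies in that range.

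Three stronger readings should be avoided.

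- From the one haematoma and two neuritis cases among 172 participants in the Safety section, a reader might infer that unintended events would be a tiny part of the total. That section also says that mostly minor and transient events occurred and does not count them, so no such share can be derived.
- Because Table 4 reports technical success per treated side, a reader might double the floor to 140. Nothing says that adverse events are counted per side.
- A reader might infer that the safety committee would be misled. Study monitoring has it review accumulating safety data after about 25% and 50% of participants are treated, and ties no threshold to the ADE count.

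This is an inexpensive improvement to the primary safety figure, and it leaves the other safety reporting as it is.

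**What to change.** 1. State before the first procedure that GON-area numbness is always recorded, and how it is coded (hypoaesthesia or anaesthesia, related to the procedure or not), so that recording is uniform from the first participant.
2. In Table 4, report the primary safety endpoint as all ADEs and also as ADEs excluding GON-area hypoaesthesia/anaesthesia. Give each as the number of events and as participants with at least one event, by CTCAE grade.
3. Show GON-area sensory loss on its own line, by grade and by whether it is still present at week 12, so that severe or persistent loss stays visible.

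The SADE count, the per-term lines and the numbness-duration endpoint stay as they are. The cost is one or two extra table lines and a coding rule. No new data are needed, no event is dropped, and the study is planned to start only in 2026.
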